|  | Grade 2 | *Hold pembrolizumab until resolves to ≤Grade 1 Discontinue if does not resolve to ≤Grade 1 within 12 weeks after last dose administration | Hold until pembrolizumab is resumed  Resume at the next lower dose level (if occurs at 140 mg once daily, discontinue).  Discontinue if pembrolizumab  is discontinued, and enter Event Monitoring |

| **System/Organ/Class (SOC)** | **ADVERSE EVENTS/SYMPTOMS** | **ACTIONS** | |
| --- | --- | --- | --- |
|  |  | **Pembrolizumab** | **Ibrutinib** |
|  | Grade ≥3 | Hold pembrolizumab. If resolves to ≤Grade 1 within 72 hours resume treatment  If not, discontinue and enter Event Monitoring | Hold until pembrolizumab resumed  Resume at the next lower dose level (if occurs at 140 mg once daily, discontinue).  Discontinue if pembrolizumab is discontinued, and enter Event Monitoring |
| Other non-laboratory Adverse Events |  | | |
|  | Grade 3 | *Hold pembrolizumab until resolves to ≤Grade 1 Discontinue if does not resolve to ≤Grade 1 within 12 weeks after last dose administration | Hold until pembrolizumab resumed Resume at the next lower dose level (if occurs at 140 mg once daily, discontinue).  Discontinue if pembrolizumab is discontinued, and enter Event Monitoring |
|  | Grade 4 | Discontinue and enter Event Monitoring | Discontinue and enter Event Monitoring |

*If ibrutinib is discontinued according to Table 8.2, continue pembrolizumab until disease progression or intolerance develops or patient refusal.

- 1. Modifications Based on Concomitant Medications and Procedures for Ibrutinib
     - **Dose Modifications for Use with CYP3A Inhibitors and Inducers**

Ibrutinib is metabolized primarily by CYP3A. Avoid co-administration with strong CYP3A4 or moderate CYP3A inhibitors and consider alternative agents with less CYP3A inhibition.

- - - - If a strong CYP3A inhibitor (eg, ketoconazole, posaconazole, indinavir, nelfinavir, ritonavir, saquinavir, clarithromycin, telithromycin, itraconazole, nefazadone, or cobicistat) must be used, reduce ibrutinib to 140 mg for the duration of the inhibitor or withhold ibrutinib treatment temporarilty (for 7 days or less). Pembrolizumab may be continued at current dose. If unable to discontinue strong CYP3A inhibitor use within 12 weeks then permanently discontinue ibrutinib.

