      - If a moderate CYP3A inhibitor (eg, erythromycin, amprenavir, aprepitant, atazanavir, ciprofloxacin, crizotinib, diltiazem, fluconazole, voriconazole, fosamprenavir, imatinib, verapamil, amiodarone, or dronedarone) must be used, reduce ibrutinib to 280 mg once daily for the duration of the inhibitor use. Avoid grapefruit and Seville oranges during ibrutinib treatment, as these are moderate inhibitors of CYP3A. (See Appendix V.)
      - No dose adjustment is required in combination with mild inhibitors.

Avoid concomitant use of system strong CYP3A inducers (e.g. carbamazepine, rifampin, phenytoin and St. John’s wort) should be avoided. Consider alternative medications with less CYP3A induction.

A list of common CYP3A inhibitors and inducers is provided in Appendix V. A comprehensive list of inhibitors, inducers, and substrates may be found at [http://medicine.iupui.edu/clinpharm/ddis/main-table/.](http://medicine.iupui.edu/clinpharm/ddis/main-table/) This website is continually revised and should be checked frequently for updates.

For the most comprehensive effect of CYP3A inhibitors or inducers on ibrutinib exposure, please refer to the current version of the IB.

- - - Concurrent use with QT Prolongation Agents

Ibrutinib is not known to prolong the QT interval, but it may affect the pharmacokinetics of other medications. Any medications known to cause QT prolongation should be used with caution; periodic ECG and electrolyte monitoring should be considered.

- - - **Dose modification for bleeding-related events (Antiplatelet Agents and Anticoagulants)**

Use ibrutinib with caution in subjects requiring anticoagulants or medications that inhibit platelet function. In an in vitro platelet function study, inhibitory effects of ibrutinib on collagen-induced platelet aggregation were observed. Supplements such as fish oil and vitamin E preparations should be avoided during treatment with ibrutinib. Bleeding events of any grade, including bruising and petechiae, occurred in subjects treated with ibrutinib. Ibrutinib should be held at least ~~3 to~~ 7 days pre- and post-surgery depending upon the type of surgery and the risk of bleeding (see section

on Dose modification for invasive procedures or surgery). Subjects with congenital bleeding diathesis have not been studied.

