# Appendix IV - Potential Drug-Drug Interactions for Ibrutinib

Ibrutinib is primarily metabolized by cytochrome P450 enzyme 3A.

**Agents That May Increase ibrutinib Plasma Concentrations (CYP3A Inhibitors)** Concomitant use of ibrutinib and drugs that strongly or moderately inhibit CYP3A can increase ibrutinib exposure and therefore strong CYP3A inhibitors should be avoided.

- If a strong CYP3A inhibitor (eg, ketoconazole, indinavir, nelfinavir, ritonavir, saquinavir, clarithromycin, telithromycin, itraconazole, nefazodone, cobicistat, and posaconazole) must be used, reduce ibrutinib to 140 mg for the duration of the inhibitor use or withhold ibrutinib treatment temporarily (for 7 days or less). Subjects should be monitored for signs of ibrutinib toxicity.
- If a moderate CYP3A inhibitor (eg, fluconazole, voriconazole, erythromycin, amprenavir, aprepitant, atazanavir, ciprofloxacin, crizotinib, diltiazem, fosamprenavir, imatinib, verapamil, amiodarone, and dronedarone) is indicated, reduce ibrutinib dose to 140 mg for the duration of the inhibitor use.
- No dose adjustment is required in combination with mild inhibitors.
- Avoid grapefruit and Seville oranges during ibrutinib treatment as these contain moderate inhibitors of CYP3A (see Section 5.3.1.2).

Avoid concomitant use of systemic strong CYP3A inducers (eg, carbamazepine, rifampin, phenytoin, and St. John’s Wort). Consider alternative agents with less CYP3A induction.

A list of common CYP3A inhibitors and inducers is provided in Appendix V. For further information, please refer to the current version of the IB and examples of inhibitors, inducers, and substrates can be found at [http://medicine.iupui.edu/clinpharm/ddis/main-table/.](http://medicine.iupui.edu/clinpharm/ddis/main-table/) This website is continually revised and should be checked frequently for updates.

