Co-administration of ketoconazole, a strong CYP3A inhibitor, in 18 healthy subjects, increased exposure (Cmax and AUClast) of ibrutinib by 29- and 24-fold, respectively. The maximal observed ibrutinib exposure (AUC) was ≤ 2-fold in 37 subjects treated with mild and/or moderate CYP3A inhibitors when compared with the ibrutinib exposure in 76 subjects not treated concomitantly with CYP3A inhibitors. Clinical safety data in 66 subjects treated with moderate (n=47) or strong CYP3A inhibitors (n=19) did not reveal meaningful increases in toxicities. Strong inhibitors of CYP3A (e.g., ketoconazole, voriconazole, posaconazole, indinavir, nelfinavir, ritonavir, saquinavir, clarithromycin, telithromycin, itraconazole, nefazadone and cobicistat) and moderate inhibitors (e.g., erythromycin, amprenavir, aprepitant, atazanavir, ciprofloxacin, crizotinib, darunavir/ritonavir, diltiazem, fluconazole, fosamprenavir, imatinib, verapamil) should be avoided (See Section 8.4).

**Agents That May Decrease ibrutinib Plasma Concentrations (CYP3A Inducers)** Administration of ibrutinib with rifampin, a strong CYP3A inducer, decreases ibrutinib plasma concentrations by approximately 90%. Avoid concomitant use of strong CYP3A inducers (eg, carbamazepine, rifampin, phenytoin and St. John’s Wort). Consider alternative agents with less CYP3A induction.

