# Appendix V - Inhibitors and Inducers of CYP3A

Inhibitors of CYP3A are defined as follows. A comprehensive list of inhibitors can be found at the following website: <http://medicine.iupui.edu/clinpharm/ddis/table.aspx> . The general categorization into strong, moderate, and weak inhibitors according to the website is displayed below. Refer to Section 8.1 on instructions for concomitant use of CYP3A inhibitors and inducers with ibrutinib.

| **Inhibitors of CYP3A** | **Inducers of CYP3A** |
| --- | --- |
| **Strong inhibitors:** | Carbamazepine |
| INDINAVIR | Efavirenz |
| NELFINAVIR | Nevirapine |
| RITONAVIR | Barbiturates |
| CLARITHROMYCIN | Glucocorticoids |
| ITRACONAZOLE | Modafinil |
| KETOCONAZOLE | Oxcarbarzepine |
| NEFAZODONE | Phenobarbital |
| SAQUINAVIR | Phenytoin |
| SUBOXONE | Pioglitazone |
| TELITHROMYCIN | Rifabutin |
| VORICONAZOLE | Rifampin |
| POSACONAZOLE | St. John’s Wort |
|  | Troglitazone |
| **Moderate inhibitors:** |  |
| Aprepitant |  |
| Erythromycin |  |
| diltiazem |  |
| Fluconazole |  |
| grapefruit juice |  |
| Seville orange juice |  |
| Verapamil |  |
| **Weak inhibitors:** |  |
| Cimetidine |  |
| **All other inhibitors:** |  |
| Amiodarone |  |
| NOT azithromycin |  |
| Chloramphenicol |  |
| Boceprevir |  |
| Ciprofloxacin |  |
| Delaviridine |  |
| diethyl-dithiocarbamate |  |
| Fluvoxamine |  |
| Gestodene |  |
| Imatinib |  |
| Mibefradil |  |
| Mifepristone |  |
| Norfloxacin |  |
| Norfluoxetine |  |
| star fruit |  |
| Telaprevir |  |
| Troleandomycin |  |

Source:[http://medicine.iupui.edu/clinpharm/ddis/table.aspx.](http://medicine.iupui.edu/clinpharm/ddis/table.aspx)

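### Section 8.3 and Appendix IV set different ibrutinib doses (280 mg and 140 mg) for the same moderate CYP3A inhibitors, and voriconazole is classed both as moderate and as strong

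*Protocol*

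**What the plan says.** The protocol deals with CYP3A inhibitors in three places. (Printed subsection numbers did not survive in the text available; 8.3 is inferred from position, after the dose-level and adverse-event tables 8.1 and 8.2.)

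- **Section 8.3** (modifications for concomitant medications) advises avoiding strong and moderate inhibitors. If a moderate one "must be used, reduce ibrutinib to 280 mg once daily for the duration of the inhibitor use". For a strong one, ibrutinib goes to 140 mg or is held for up to 7 days, and "If unable to discontinue strong CYP3A inhibitor use within 12 weeks then permanently discontinue ibrutinib". Voriconazole is among the moderate examples. The reader is sent to Appendix V for a list of common inhibitors.
- **Appendix IV** (drug interactions) says that if a moderate inhibitor "is indicated, reduce ibrutinib dose to 140 mg for the duration of the inhibitor use". Voriconazole is again a moderate example. Further on, the same appendix lists "Strong inhibitors of CYP3A (e.g., ketoconazole, voriconazole, posaconazole, indinavir" and others, which makes voriconazole strong, and ends that guidance with "should be avoided (See Section 8.4".
- **Appendix V** prints "VORICONAZOLE" under its strong inhibitors. For what to do it says "Refer to Section 8.1 on instructions for concomitant use of CYP3A inhibitors and inducers with ibrutinib".

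Appendix IV is text that staff will use. Section 15 refers to it under ibrutinib's potential drug interactions and again in the nursing guidelines.

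**The concern.** Two prescribers, each following the protocol, could give the same patient doses that differ by a factor of two. A clinician who starts from Section 8 arrives at 280 mg. One who starts from Section 15 and follows its pointer arrives at 140 mg. Several of the example drugs are antimicrobials or cardiac drugs (fluconazole, ciprofloxacin, erythromycin, diltiazem, verapamil, amiodarone).

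Ibrutinib dose is the quantity this trial was rebuilt to determine. Section 1 reports that 560 mg with pembrolizumab was followed by Grade 3 rash in both of the first two patients, after which the study became a dose-finding design. That history is context only: it mentions no CYP3A inhibitor, and both disputed doses lie below the 420 mg MTD.

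The class of voriconazole adds a second ambiguity. It bears on the on-study dose, on the permanent stop, and on the registration exclusion for strong inhibitors taken in the previous 7 days, which cites no list.

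**Working it through.** **1. Is it the same rule for the same drugs?** Both bullets apply when a moderate inhibitor has to be given. Their examples, sorted alphabetically, are amiodarone, amprenavir, aprepitant, atazanavir, ciprofloxacin, crizotinib, diltiazem, dronedarone, erythromycin, fluconazole, fosamprenavir, imatinib, verapamil and voriconazole. That is 14 in Section 8.3 and 14 in Appendix IV, and the two sets are identical. The texts therefore cannot be reconciled as rules for different drugs.

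**2. How far apart are the doses?** 280 / 140 = 2. Reduction = (current dose − target) / current dose:

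| Current dose | Why a patient may be on it | Section 8.3 (280 mg) | Appendix IV (140 mg) |
|---|---|---|---|
| 420 mg | MTD, expansion starting dose | (420 − 280)/420 = 33% | (420 − 140)/420 = 67% |
| 280 mg | Table 8.1 level −1, or the Section 16 safety-check fallback | 0% | (280 − 140)/280 = 50% |
| 140 mg | Table 8.1 level −2 | 0% | 0% |

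The last row is 0% under both rules because an instruction to reduce cannot raise a dose, and Section 7 bars escalation within a patient. These are nominal doses; nothing is inferred about exposure.

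**3. Does any text settle which rule governs?**

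- Appendix V points to Section 8.1 and Appendix IV to Section 8.4. The numbers differ, and neither pointer says which dose prevails.
- Both places refer to the Investigator's Brochure for further information, but not to resolve a conflict on dose.
- The Appendix IV list says of grapefruit and Seville oranges "as these contain moderate inhibitors of CYP3A (see Section 5.3.1.2", but Section 5 of this protocol is Grouping Factors and contains only the entry None. This suggests, without proving, that the appendix text was not fully adapted to this trial.

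**4. How is voriconazole classed?** Intersecting the 14 moderate examples with the strong lists in the later part of Appendix IV and in Appendix V leaves exactly one drug, voriconazole.

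| Text | Class of voriconazole |
|---|---|
| Section 8.3 | moderate |
| Appendix IV, dosing bullets | moderate |
| Appendix IV, later paragraph | strong |
| Appendix V | strong |

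The consequences are as follows.

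- *Dose under Section 8.3:* 280 mg if moderate; 140 mg, or a hold of up to 7 days, if strong.
- *Permanent stop:* the 12-week rule in Section 8.3 applies only if strong.
- *Washout before registration:* the criterion names no list, so the class has to be inferred.
- *Pre-registration exclusion for continuous strong-inhibitor use:* clear, because it cites Appendix V.

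**5. Do the lists differ in other ways?** Appendix V puts amiodarone, ciprofloxacin and imatinib under its residual category of other inhibitors, where the dosing bullets call them moderate. So voriconazole is the only moderate-versus-strong conflict among the 14, but not the only mismatch between the lists.

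**The case against.** The strongest reply is that the structure of the protocol already favours Section 8.3. Section 8 is the dose-modification section, both appendices point back into it, and Section 15 cites Appendix IV mainly for which agents to avoid. A careful reader would probably take 280 mg as operative. That makes divergent prescribing less likely, but it is an inference. Appendix IV still gives an unqualified dosing instruction, and nothing subordinates it.

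On the washout, the neighbouring pre-registration exclusion relies on Appendix V, so reading voriconazole as strong is reasonable there too. This is fair, and it makes the washout the weakest of the three consequences. The on-study dose and the 12-week stop remain open, because Section 8.3 itself names voriconazole as moderate and then refers to a list that calls it strong.

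The practical reach is also limited, and this stands:

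- Moderate inhibitors are to be avoided anyway, and the protocol gives no frequency for unavoidable use.
- At Amendment 6 (October 2020) at most 10 further patients were planned at the MTD, with 5–6 months of accrual expected. The current text is Amendment 8 (November 2022), so on the planned timetable mainly patients still on treatment would be affected. Actual accrual is not stated.
- Appendix IV reports an AUC increase of at most 2-fold in 37 subjects on mild or moderate inhibitors, and no meaningful rise in toxicities among 66 subjects on moderate (47) or strong (19) inhibitors. Section 15 accepts a doubling of mean exposure with food. The protocol does not say that the Appendix IV subjects also received pembrolizumab.

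**Conclusion.** The inconsistency is real and should be fixed. Two current instructions cover the same trigger and the same 14 drugs, they differ two-fold in dose, and no stated precedence resolves them. It matters most for a patient already at 280 mg, where one text requires no change and the other halves the dose. The voriconazole conflict is separate and affects one drug of the 14.

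The conclusion rests on reading the current text alone. It makes no claim about which dose is correct, about ibrutinib exposure, or about how often the situation arises, since the protocol does not settle any of these. It does not touch the sample size or the rule of two responses in 14 patients.

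**What to change.** Issue a text amendment and a memo to prescribers that:

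1. state a single ibrutinib dose for moderate CYP3A inhibitors in Section 8.3, with the sponsor confirming 280 mg or 140 mg against the current Investigator's Brochure;
2. give voriconazole one class throughout, so that its dose, the 12-week stop and the 7-day washout all follow from it;
3. make Appendices IV and V agree with Section 8.3, or replace their dosing text with a reference to it under its correct number, and remove the pointer to Section 5.3.1.2.

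No extra rule against raising a dose is needed, because Section 7 already covers that. The cost is editorial: design, sample size and analysis are unchanged.

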# Protocol Treatment

- 1. Treatment Schedule

Use actual weight or estimated dry weight if fluid retention Cycle 1 treatment = 28 days

All subsequent treatment cycles = 21 days (±3 days)

| Drug | Dose | Treatment | Retreatment |
| --- | --- | --- | --- |
| Ibrutinib | assigned at registration | PO daily (Day 1 to 28  of Cycle 1, then Day 1- 21* on subsequent cycles) | Every 21 days  (±3 days)  until confirmed progression |
| Pembrolizumab | 200 mg | IV injection on Day 8 of Cycle 1 and then Day 1 of each  subsequent cycle | Every 21 days (±3 days) until confirmed progression |

* Patients should receive a sufficient quantity of ibrutinib to last until the next scheduled treatment visit.

- 1. Determination of Maximum Tolerated Dose (MTD)
  2. Dose Escalation Scheme

| Dose level | Ibrutinib** |
| --- | --- |
| -1 | 140 mg |
| 0* | 280 mg |
| 1 | 420 mg |

* Starting dose level

** If the patient has clinical or laboratory evidence of liver failure during the treatment, then calculate the Child-Pugh score and adjust the ibrutinib dose (see Table 8.3).

NOTE: Doses will not be escalated in any individual patient.

- 1. MTD Determined

As of MCCC Amendment 6, the MTD has been determined to be Dose Level 1. Dose Level 1 will be used for the expansion cohort.

- 1. Dose Limiting Toxicities

Dose limiting toxicities (DLT) are defined to be:

| ***Toxicity*** | ***DLT Definition*** |
| --- | --- |
| Hematologic | Grade 4 ANC, Grade 4 Hgb, or PLT <25,000 |
| Renal | Serum creatinine ≥2 times baseline |
| Neurologic | ≥Grade 2 neurosensory or neuromotor toxicity |
| Other nonhematologic | ≥Grade 3 per NCI Common Terminology Criteria for Adverse Events (CTCAE) version 4.0* |

*Grade 3 rash or fever despite maximal supportive treatment(s) will be considered dose-limiting; all grade 4 rash and fever will be considered a DLT.

The maximum tolerated dose is defined as the highest dose level among those tested where at most one out of 6 patients develops a DLT prior to the start of their second cycle of treatment and the next highest dose level is such that 2 out of a maximum of 6 patients treated at this dose level developed a DLT prior to the start of their second cycle of treatment.

- 1. Dose escalation plan

NOTE: As of MCCC Amendment 6, the MTD has been determined to be Dose Level 1. A minimum of 2 or a maximum of 6 patients will be accrued to a given dose level.

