***ALERT:* ADR reporting may be required for some adverse events (See Section 10)**

- 1. Dose Levels

(Based on Adverse Events in Table 8.2)

| **Dose Level** | **Ibrutinib** | **Pembrolizumab** |
| --- | --- | --- |
| 1* | 420 mg PO once daily | 200 mg IV |
| -1 | 280 mg PO once daily | NA |
| -2 | 140 mg PO once daily | NA |

*Dose level 1 refers to the starting dose.

- 1. Dose Modifications Based on Adverse Events

NOTE: These modifications only apply if the adverse event is **possibly**, **probably**, or

**definitely** related to study treatment

| **System/Organ/Class (SOC)** | **ADVERSE EVENTS/SYMPTOMS** | **ACTIONS** | |
| --- | --- | --- | --- |
|  |  | **Pembrolizumab** | **Ibrutinib** |
| Blood and lymphatic | **Anemia** | | |
| system disorders | Grade 4 | Hold pembrolizumab until  ≤Grade 2 and etiology is  determined  If anemia is immune-mediated (at least possibly related to pembrolizumab), discontinue pembrolizumab | Discontinue ibrutinib |
|  | **Febrile neutropenia (See also Investigations/Neutrophil count decreased)** | | |
|  | Grade 3 | Hold until symptoms resolve to  ≤Grade 1 | Hold until symptoms resolve to  ≤Grade 1;  Resume at the next lower dose level (if occurs at 140 mg once daily, discontinue) |
|  | Grade 4 | Hold until symptoms resolve to  ≤Grade 1 | Discontinue ibrutinib |
| Cardiac disorders | **Cardiac arrythmias** | | |
|  | Grade 3 | Continue pembrolizumab | Hold until symptoms resolve to  ≤Grade 1, then resume Resume at the next lower dose level  (if occurs at 280 mg once daily or lower, discontinue ibrutinib) |
|  | Grade 4 | Discontinue and enter Event Monitoring. | Discontinue and enter Event Monitoring |

| **System/Organ/Class (SOC)** | **ADVERSE EVENTS/SYMPTOMS** | **ACTIONS** | |
| --- | --- | --- | --- |
|  |  | **Pembrolizumab** | **Ibrutinib** |
| Cardiac disorders | **Cardiac failure** (not due to immune-related myocarditis) | | |
|  | Grade 2 | Hold until symptoms resolve to  ≤Grade 1, then resume | Hold until symptoms resolve to  ≤Grade 1;  Resume at the next lower dose level (if occurs at 140 mg once  daily, discontinue) |
|  | Grade 3 or 4 | Discontinue and enter Event Monitoring. | Discontinue and enter Event Monitoring. |
| Cardiac disorders | **Myocarditis** | | |
|  | Grade 2+ | Discontinue and enter Event Monitoring. | Discontinue and enter Event Monitoring. |
| Endocrine Disorders | **Symptomatic Hypophysitis** | | |

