- For subjects with existing chronic mild hepatic impairment (Child-Pugh class A) at enrollment, the starting dose has to be adjusted to a level of 280 mg daily (two capsules).
- For subjects who develop mild hepatic impairment while on study (Child-Pugh class A), the recommended dose reduction for ibrutinib/placebo is to a level of 280 mg daily (two capsules) unless lower doses had already been implemented.
- For subjects who develop moderate hepatic impairment while on study (Child-Pugh class B), the recommended dose reduction is to a level of 140 mg daily (one capsule).
  1. Overdose
- Subjects who develop severe hepatic impairment (Child-Pugh class C) must hold study drug until resolved to moderate impairment (Child-Pugh class B) or better.

Subjects who develop acute hepatic toxicity with liver enzymes Grade 3 or higher while on study should be managed per standard dose modification guidelines in Section 8.

There is no specific experience in the management of ibrutinib overdose in patients. No maximum tolerated dose (MTD) was reached in the Phase 1 study in which subjects received up to 12.5 mg/kg/day (1400 mg/day). Healthy subjects were exposed up to single dose of 1680 mg. One healthy subject experienced reversible Grade 4 hepatic enzyme increases (AST and ALT) after a dose of 1680 mg. Subjects who ingest more than the recommended dosage should be closely monitored and given appropriate supportive treatment.

Refer to Section 10.0 for further information regarding AE reporting.

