- If none of these 3 additional patients develops a DLT during the first cycle of treatment, enrollment to this dose level will be closed and enrollment will reopen at next higher dose level. If there are no other higher dose levels to be tested, this will be considered the MTD
  1. Study Design – Expansion Cohort (Treated at MTD)

Acknowledging both the short term aspect of the primary endpoint of the study and that 18 patients may be enrolled, we have chosen a phase II study design proposed by Gehan30. Two (2) responses in 14 eligible patients having initiate treatment will be considered indicative of promising activity and further study in a phase 2 study. According to Gehan, if a drug were 20 percent effective or more, there would be a 95% chance that one or more successes would be obtained in 14 patients^30^.

Gehan’s approach calculated cumulative probability of observing at most x successes in N patients (i.e., assuming a binomial distribution) assuming the true success rate is P.

Assuming true success (response) proportion in 14 patients is P=20%:

| If the number of responses (x) observed… | Then the probability of observing  ≤ x responses is less than or equal  to… |
| --- | --- |
| 0 | 0.044 |
| 1 | 0.198 |
| 2 | 0.448 |
| 3 | 0.698 |

Assuming true success (response) proportion in 14 patients is P=30%:

| If the number of responses observed… | Then the probability of observing  ≤ x responses is less than or equal  to… |
| --- | --- |
| 0 | 0.007 |
| 1 | 0.047 |
| 2 | 0.161 |
| 3 | 0.355 |

Two planned safety checks will occur after 3 and 6 patients have completed their first cycle of treatment. If we observe DLT(s) at either review of the data (1 DLT in the first 3 patients or 2 DLTs in the first 6 patients), we will drop the starting dose level to 280 mg and continue with the remainder of the study. Only one reduction in the starting dose level will be allowed. All data will be summarized by assigned starting dose level and by prior ICI therapy status.

- 1. Sample Size

Enrollment and anticipated number of patients, phase of study:

- - - Prior to MCCC Amendment #2, two patients were enrolled and the study was stopped due to toxicity. The study reopened was modified to a phase I (vs phase II).
    - Phase I - During the dose escalation phase, a minimum of 9 and a maximum of 18 patients is anticipated. Enrollment was completed prior to MCCC Amendment #6 (11 patients).

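### For a moderate CYP3A inhibitor that must be used, Section 8.3 sets ibrutinib at 280 mg and Appendix IV at 140 mg, and nothing says which governs

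*Protocol*

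**What the plan says.** Section 8.3 (Modifications Based on Concomitant Medications and Procedures for Ibrutinib) opens with a general instruction: "Avoid co-administration with strong CYP3A4 or moderate CYP3A inhibitors and consider alternative agents with less CYP3A inhibition". If a moderate inhibitor must nevertheless be used, the prescriber is to "reduce ibrutinib to 280 mg once daily for the duration of the inhibitor use".

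Appendix IV (Potential Drug-Drug Interactions for Ibrutinib) covers the same case. Its bullet says that if a moderate inhibitor "is indicated, reduce ibrutinib dose to 140 mg for the duration of the inhibitor use".

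Patients can be at 280 mg by three routes:

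- It was Dose Level 0 in the escalation phase.
- It is the first reduction step below 420 mg in the Section 8.1 table. Most toxicity entries in Section 8.2 read: "Resume at the next lower dose level (if occurs at 140 mg once daily, discontinue".
- It is the expansion cohort's fallback. If the safety checks in Section 16.3 are triggered, "we will drop the starting dose level to 280 mg and continue with the remainder of the study".

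Section 7.2 adds, under the escalation table: "Doses will not be escalated in any individual patient".

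**The concern.** A dose-modification rule has to give one dose for one situation. Here two operative passages give two doses, and neither is an amendment log or superseded text.

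The conflict reaches patients on the planned regimen. Expansion patients start at 420 mg, and eligibility bars only strong inhibitors (Sections 3.2 and 3.4), so someone taking a moderate one may enter. Patients at 280 mg are fewer, but for them the question is whether the dose changes at all. Some will be at 280 mg because they did not tolerate 420 mg, and for them Section 8.3's instruction has no effect.

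At stake is dosing consistency and the safety of individual patients. No statistical property of the design is involved.

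**Working it through.** **Step 1: do the two rules cover the same drugs?** Section 8.3 lists erythromycin, amprenavir, aprepitant, atazanavir, ciprofloxacin, crizotinib, diltiazem, fluconazole, voriconazole, fosamprenavir, imatinib, verapamil, amiodarone and dronedarone. That is 14 drugs. Appendix IV lists 14 in a different order, and compared as sets the two lists are identical. Scope does not explain the difference.

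**Step 2: do the triggers differ?** Section 8.3 applies when the drug must be used, Appendix IV when it is indicated. A drug that must be used is also indicated, so every Section 8.3 case falls under Appendix IV too.

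**Step 3: is the strong-inhibitor rule also in conflict?** No. Both places give 140 mg or a hold of up to 7 days. Only the moderate rule conflicts.

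**Step 4: what dose results?** Reading both texts as reductions, new dose = min(current dose, stated dose), and reduction = 1 − new/current.

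| Current dose | Section 8.3 (280 mg) | Appendix IV (140 mg) |
| --- | --- | --- |
| 420 mg | 280 mg; 1 − 280/420 = 33% | 140 mg; 1 − 140/420 = 67% |
| 280 mg | 280 mg; 0% | 140 mg; 1 − 140/280 = 50% |
| 140 mg | 140 mg; 0% | 140 mg; 0% |

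For anyone at 420 or 280 mg the two rules differ by 280/140 = 2.0. At 140 mg they agree.

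**Step 5: does any text settle precedence?**

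- Section 15.1 (Potential Drug Interaction) sends the reader to Appendix IV. Its nursing guidelines name Section 8.2 and Appendix IV.
- Appendix IV sends the reader to Section 8.4, which in the running order of headings is Overdose.
- Appendix V sends the reader to Section 8.1, the dose-level table, which has no inhibitor rule.
- Section 8.3 cites the Investigator's Brochure for the effect on exposure, and Appendix IV cites it for further information. Neither says that it overrides the stated dose.

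The pointers run in both directions and two land in the wrong place. None ranks the texts.

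**Step 6: voriconazole.** Both moderate-inhibitor bullets list it as moderate. A later paragraph of Appendix IV and the table in Appendix V list it as strong. Under Section 8.3 the class decides between 280 mg and 140 mg (or a hold), so harmonising the moderate dose alone would leave this drug unresolved.

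**The case against.** The best reply is that the body outranks an appendix, and that both appendices point back to Section 8. Appendix IV's Section 8.4 looks like an outdated number for the concomitant-medication section, since the Test Schedule uses the same number for the biopsy hold, which sits there. This leans towards 280 mg. It is an inference, though, and Section 15.1 points the other way. A prescriber who follows that pointer finds 140 mg, stated without qualification.

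The second reply is that the case is uncommon, and that stands. These drugs are to be avoided, a patient at 280 mg usually needs a prior toxicity reduction first, and the document gives no frequency for any step.

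Some stronger readings are tempting and should not be drawn:

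- *That Section 8.3 takes patients back to the dose abandoned for rash.* Doubling 280 mg gives 560 mg, the dose dropped after Grade 3 rash in both of the first two patients. This assumes proportional exposure below 420 mg (Section 15.1 states it only for 420 to 840 mg). It also takes a rise of 2-fold, the upper limit Appendix IV reports for mild and moderate inhibitors pooled. Appendix IV reports no meaningful increase in toxicities in 66 subjects on moderate or strong inhibitors, and Section 15.1 accepts a mean doubling of exposure with food. Two patients and a maximum do not establish a hazard.
- *That different sites will dose differently.* Treatment must commence at one named centre (Section 6). Only divergence between readers is supported.
- *That Section 8.3 would raise a patient from 140 to 280 mg.* The instruction is to reduce, and Section 7.2 bars escalation within a patient. This is a clarity point only.
- *That 140 mg, or 280 mg, is the correct figure.* The document does not show which was intended.

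**Conclusion.** The contradiction is real and plain on the page: two current instructions, the same 14 drugs, doses of 280 and 140 mg, and no rule of precedence. The difference is two-fold for any patient at 420 or 280 mg, and at 280 mg it decides whether there is a reduction at all. This rests on the text and simple arithmetic, with no pharmacokinetic assumption.

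It should be corrected, but its importance is limited. The rule applies only when a drug that should be avoided has to be given. Section 16.4 planned at most 10 additional patients at Amendment 6. The maximum tolerated dose definition, the response endpoint, the sample size and the analysis are untouched.

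**What to change.** State one identical rule in Section 8.3 and Appendix IV. A workable version is one dose level down while the moderate inhibitor is used:

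- 420 mg goes to 280 mg, as Section 8.3 now has it.
- 280 mg goes to 140 mg, as Appendix IV now has it.
- 140 mg stays at 140 mg with monitoring, or ibrutinib is withheld. The dose is never increased.

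The sponsor should confirm the 420 mg target against the current Investigator's Brochure, because the protocol does not show which figure was meant. For patients already on a lower dose, the Child-Pugh class A bullet in Section 8.3 has usable wording: "unless lower doses had already been implemented".

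In the same edit, place voriconazole in one class throughout Section 8.3, Appendix IV and Appendix V, and correct the inhibitor cross-references in Appendix IV (Section 8.4) and Appendix V (Section 8.1) to Section 8.3.

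The cost is a wording amendment. The clinical downside is somewhat lower ibrutinib exposure in a few patients during inhibitor use. For a 280 mg patient moved to 140 mg, exposure could fall to about half the intended level if the inhibitor had little effect, assuming exposure is proportional to dose in that range.
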